**Fig 2 pone.0291289.g002:**
[figure not shown]
Participants’ setup. The positions for the three grades of wearables and reflective markers for 3D motion capture are shown.

#### Reference standard: Force plate system

Two staggered 0.5-m-long force plates (AMTI, Watertown, MA, USA), sampling at 1000 Hz will be embedded in the middle of a 15m walkway.

#### Wearables

With many wearables available, it is difficult to choose the most suitable [21]. Accordingly, this protocol includes options from three categories to suit varying user needs: (1) modifiable research-grade; (2) attainable (low-grade) commercial with proprietary software; and (3) novel multimodal high-end system [18]. Accordingly, the three wearable types presented here are: research grade AX6 (Axivity, https://axivity.com/), entry-level commercial DorsaVi ViMove2 (DorsaVi, www.dorsavi.com/vimove/) and advanced multimodal DANU System (DANU Sports, www.danusports.com/).

Typically, research-grade devices require users to have specialist / technical knowledge due to the tendency of devices to provide the raw data only. Therefore, the user often needs to create and implement algorithms to achieve tangible outcomes. However, these devices offer the flexibility to define wear location and creation of novel outcomes [27]. Consumer level / commercial wearables with proprietary software are sought to be user-friendly, requiring little technical knowledge or experience, producing outcomes automatically. For these devices, it is often unclear how reference limits are set, or established for such functions [27]. Rather than showing the raw data collected by the wearable, users typically export information after it has been analysed and filtered through an algorithm. More advanced multi-modal devices (e.g., combined IMU and pressure sensors in a single system) offer numerous sensing capabilities with multiple algorithms that are enabling laboratory grade sensing in any location. Accordingly, the integrated sensor arrangement enables a comprehensive assessment of running gait (i.e., spatiotemporal, and kinetic outcomes) and attempt to offer the advantages of both research-grade and commercial wearables.

*Axivity AX6*. The AX6 (2.3 × 3.3 × 0.8 cm, 11g) consists of a configurable tri-axial accelerometer (±2, ±4, ±8, ±16g) and tri-axial gyroscope (±125 –±2000°/s) with variable sampling capabilities (12.5Hz - 1600Hz), set via a configuration proprietary software (OmGUI). Here, the device will be configured to a sampling rate of 200Hz, ±16g accelerometer and ±2000°/s gyroscope. Although it can be worn on any anatomical landmark, due to lack of proprietary analytical software, it will be secured onto the talus joint of each shoe with medical tape, Fig 3. The AX6 is considered a valid technology which can capture data in controlled and free-living environments [28]. Data are recorded and stored locally on the device and download via OmGUI upon completion of recording.

**Fig 3 pone.0291289.g003:**
[figure not shown]
Axivity AX6.

*DorsaVi ViMove2*. The DorsaVi ViMove2 consists of two IMUs modules, each comprising a tri-axial accelerometer (±16g) with tri-axial magnetometer and tri-axial gyroscope (±250°/s), sampling at 100Hz. Modules will be placed onto the anterior surface of the mid-shank of the right and left tibia, as per manufacturer’s guidelines (Fig 4) [29]. Tibia sensor placement is based on the anthropometric measurement of height and a ruler is used to measure exact placement, which is the midpoint between the knee and ankle along the anterior surface of the tibia [30]. After placement of bilateral tibia sensors, the DorsaVi ViMove2 is calibrated via its ViPerform software. Data are transmitted through wireless channel to a recording and feedback device, from which data can be offloaded onto PC for further analysis.

**Fig 4 pone.0291289.g004:**
[figure not shown]
DorsaVi ViMove2.

*DANU sports system*. The DANU Sports System (Fig 5) is a pair of textile socks, to be worn on both feet. Each sock contains 15 silicone based capacitive pressure sensors, and an IMU module attached onto the anterior surface of the mid-shank of tibia. Each IMU module is Bluetooth enabled for data transmission and is comprised of two configurable tri-axial accelerometers (Accelerometer 1 ±2g, ±16g, and ±32g, Accelerometer 2 ±50g, ±100g, and ±200g), gyroscope (±2000°/s), magnetometer, and with variable sampling rates (60 – 250Hz). The IMU module includes in-built memory for data collection. For this protocol, the DANU Sports System will be configured to a default sampling rate of 250Hz, ±16g, ±50g accelerometers and ±2000°/s gyroscope. Data is collected via Bluetooth on Apple devices 2018 or later (iPad or iPhone devices are required to have at least Bluetooth 5.0 connectivity), and data processing is run through a custom-made Apple application for real-time feedback and visualisation.

**Fig 5 pone.0291289.g005:**
[figure not shown]
DANU sports system.

### Data collection

Prior to data collection, all participants regardless of study arm (laboratory or real-world) will complete a questionnaire to provide information pertaining to their demographics, lifetime athletic injury history, medical history, sporting pursuits and running personal bests (S1 Appendix). Injury will be classified as “any muscle, bone, tendon or ligament pain in the lower back/legs/knee/foot/ankle that caused a restriction or stoppage of running (distance, speed, duration or training) for at least 7 days or 3 consecutive scheduled training sessions, or that required the runner to consult a physician or other health professional” [31–33].

#### Laboratory testing

Laboratory testing will be conducted at the biomechanics laboratory Northumbria University, Newcastle upon Tyne, United Kingdom. Within the controlled laboratory environment, we will conduct a concurrent data collection with the multimodal, commercial, and research-grade wearables to determine their validation and reliability for running gait analysis compared to laboratory reference standards (3D motion capture and force plates). Recruitment for the laboratory testing began in September 2021 with an expected end date September 2023.

*Participants*. Within the laboratory testing 40 individuals will be recruited, specifically 20 with and 20 without a history of previous lower limb injury (but fully recovered at time of assessment and able to run safely, in line with inclusion / exclusion criteria).

*Laboratory reference set-up*. As previously described, a 3D motion capture and force plate system will be used as the ‘gold-standard’ reference measures.

*Running procedures*. All participants will run overground and, on a treadmill, (Spirit fitness XT485). Participants will be provided with a standardised, neutral cushioning running shoe (Saucony Guide Runner) to wear during testing in order to remove bias [34]. Prior to testing, participants will run on the treadmill at a comfortable speed for a warm-up and to familiarise themselves with running on a treadmill. Participants will be allowed breaks at any point or permitted to abort the trial at any time. For the overground segment, participants will run at a comfortable self-selected speed overground for 10m intermittently, where they will be asked to foot-strike two staggered force plates in the middle of the run (~5m point). Practice trials will be performed prior to data collection to allow participants to adjust their start position to strike the force plates correctly. A total of five successful recordings for each of the left and right leg will be captured. For the treadmill segment, participants will be asked to run at five speeds, four of these speeds will be standardised (i.e., 8, 10, 12 and 14 km/hr) and one speed will be their self-selected speed. Self-selected speed will be determined by the participant’s 5km personal best. The order of speed will be consistent across participants, starting at the slowest speed and progressing to the fastest to ensure the safety of participants. Data will be collected for 60s at each speed.

*Initial data processing*. Data will be collected simultaneously by the measurement systems, at the commencement and conclusion of each task, the time will be synchronized with a laptop and recorded by the assessor (i.e., time-stamp extraction). At the end of each testing session, the wearable and reference device data will be download onto a computer and stored in secure servers for further data processing and analysis.

#### Reliability testing

Each participant will complete the protocol in the same format in a repeated-measures design, approximately one week after the first session to establish the test-retest reliability.

#### Real-World environment testing

Data from the novel multimodal, commercial, and research-grade wearables will be collected within real-world environments to test the clinical / performance validity of the wearables (i.e., can they differentiate or provide meaningful data on relevant populations). Recruitment for the real-world environment testing began in June 2023 with an expected end date October 2023.

*Participants*. Within the real-world environment testing 40 individuals, specifically novice/amateur (n = 20) and expert/sub-elite (n = 20) running performance level. Performance level will be based on their 5km running time (i.e., age graded performance % [35]).

*Wearable location*. Each participant will be equipped with the DANU Sports System (socks on both feet), two Axivity AX6 sensors attached to the shoelaces and two DorsaVi ViMove2 sensors on the tibia.

*Running procedures*. All participants, regardless of performance level, will be asked to complete a 5km run on a standardised route in North-East England. The course will be run on a mixture of trail paths and concrete paths, with 174ft elevation gain throughout. Information about conditions (e.g., environment and shoes) and objective load data (e.g., time and pace) will be collected. Participants will wear their own running shoes.

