To examine the analytical (concurrent) validation of running gait outcomes measured in real-world settings from the various grades of wearables in all real-world testing participants (n = 40), we will compare outcomes across the wearable devices (research, commercial and novel multi-modal) through widely used measures of agreement. The absolute difference, r, ICC, the level of agreement through the Bland Altman plots, 95% LoA, RMSEs will be calculated to evaluate agreement between outcomes generated by each wearable [48].

*Exploratory clinical validation analysis*. To provide an initial exploration of clinical (performance) validation, we will investigate group difference and relationships with clinically (or performance) relevant measures. For group differences (e.g., previous injury history or performance level), analysis of co-variance (ANCOVA), will be conducted to assess for differences between groups (injured vs non-injured, or elite vs novice) in the individual running gait outcomes (e.g., ground contact time etc.) from the novel multimodal, commercial and research-grade wearable devices during the running tasks, while controlling for demographics that are significantly related to the running gait outcomes. Relationships between running gait outcomes and demographic variables (e.g., sex, age, height, weight etc.) within groups (injured vs non-injured, or elite vs novice) will be completed through Pearson correlations within each grade of wearable device (research, commercial, multimodal).

To examine the usability of the wearable devices the SUS scores for each wearable will be calculated and visualised. To investigate differences in participant perception of the usability for each grade of wearable, separate analysis of variance (ANOVA) tests will be performed. The ANOVAs will determine the differences between the SUS scores within the different device grades between participant groups (e.g., injury history, performance level). The relationships between the SUS scores, demographics (e.g., sex, age, age-grade performance), and wearables characteristics (e.g., price, weight, and battery life) will be explored using Pearson correlations [39]. The strength of the correlation will be assessed based on Cohen’s criteria: correlations < 0.30 are considered small, correlations between 0.30 and 0.50 will be considered medium, and correlations > 0.50 are considered strong [53].

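### Gait outcomes in the real-world arm are related to performance only through an elite-versus-novice factor; a regression on the age-graded 5 km percentage across all 40 runners could be added cheaply

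*Protocol article*

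**What the plan says.** Under Real-World environment testing, the protocol article recruits 40 runners as two quotas, "specifically novice/amateur (n = 20) and expert/sub-elite (n = 20) running performance level", and gives the basis for the classification: "Performance level will be based on their 5km running time (i.e., age graded performance % [35". The basis is a percentage for each runner. The text gives no cut-point and no gap between the groups.

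Under Statistical analysis, Exploratory clinical validation analysis, an ANCOVA examines "differences between groups (injured vs non-injured, or elite vs novice) in the individual running gait outcomes", adjusting for demographics found to be related to the outcome. The other planned gait analysis is correlational: "Relationships between running gait outcomes and demographic variables (e.g., sex, age, height, weight etc.) within groups". Age-graded percentage is not named in that list, and the correlations are confined to each group.

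For usability there are two analyses. One is by group: "The ANOVAs will determine the differences between the SUS scores within the different device grades between participant groups (e.g., injury history, performance level". The other uses the continuous score: "The relationships between the SUS scores, demographics (e.g., sex, age, age-grade performance), and wearables characteristics".

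The Outcome measures section makes the gait outcomes primary and usability secondary.

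**The concern.** A two-level factor treats all runners within a group as having the same performance level, although their percentages are known. If a gait outcome changes roughly in proportion to performance, the within-group part of that relation goes unused. The secondary usability outcome has a planned analysis on the continuous score; the primary gait outcomes have none across the whole sample.

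At stake is the performance half of the exploratory clinical validation. With 40 runners, a device whose outcome does track performance is more likely to be reported as showing no difference. The size of a group contrast also depends on where the quotas happened to fall. That matters because the Sample size calculation section expects later studies to take their sample sizes from these findings.

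**Working it through.** **The plan's own figure.** The Sample size calculation section supports 20 per group by rule of thumb. It gives no effect size, SD or power, so the figure cannot be reproduced; 20 + 20 = 40 is consistent. What 20 per group can detect at 80% power, two-sided 5%: d = √[2(1.960 + 0.842)²/20] = √(15.70/20) = 0.886 by the normal approximation, or 0.91 by the t-test.

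**Share of the score carried by the group factor.** For a normal score split at its median, the squared correlation between score and group is 2/π = 0.637. On that basis 40 runners act like 40 × 0.637 ≈ 25, and a correlation is attenuated by √0.637 = 0.80. If the groups are drawn from separated parts of the scale, the simulated share is about 0.82 (outer thirds), 0.88 (outer quarters) or 0.95 (outer tenths).

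**Check at one point.** Take a correlation of 0.4 and a median cut. The mean difference is 2 × 0.4 × 0.798 = 0.638. The within-group SD is √(1 − 0.16 × 0.637) = 0.948. So d = 0.638/0.948 = 0.67, short of the 0.91 needed for 80% power.

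**Simulated power.** Assumptions (none is in the article): normal score, outcome = r × score + √(1 − r²) × noise, r the correlation in an unselected running population, no covariates, 20 per group, two-sided 5%, 38 df, 40,000 replicates. Cells show group factor vs continuous percentage, with the difference in points.

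| How the two groups are drawn | r = 0.3 | r = 0.4 | r = 0.5 |
|---|---|---|---|
| Meet at the median | 32.7 vs 48.3 (15.6) | 54.7 vs 74.8 (20.1) | 76.9 vs 92.8 (15.9) |
| Bottom 40% vs top 40% | 45.6 vs 57.5 (11.9) | 71.3 vs 83.5 (12.2) | 90.6 vs 96.8 (6.2) |
| Outer thirds | 55.4 vs 64.5 (9.1) | 81.5 vs 89.1 (7.6) | 96.1 vs 98.6 (2.5) |
| Outer quarters | 68.1 vs 74.5 (6.4) | 91.8 vs 95.1 (3.3) | 99.2 vs 99.7 (0.5) |
| Bottom half vs top tenth | 68.5 vs 75.1 (6.6) | 91.9 vs 95.5 (3.6) | 99.3 vs 99.8 (0.5) |

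Type I error was about 5% for both analyses. A separate simulation with 20,000 replicates covered the median, outer-third and outer-quarter rows and agreed within about two points. It also gave 92.1 vs 93.6 for outer tenths at r = 0.3, a loss of 1.5 points.

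**Do the planned within-group correlations fill the gap?** No. Within groups, only the remainder of the score's variance is available: 1 − 0.637 = 36% at a median cut and 1 − 0.82 = 18% for outer thirds, divided between two samples of 20.

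**Why a slope rather than a correlation.** Sampling the outer thirds raises the variance of the score from 1 to 1 + 0.4307 × 0.3636/(1/3) = 1.47. A population correlation of 0.30 then appears as 0.30 × √1.47 / √(0.09 × 1.47 + 0.91) = 0.36. The regression slope is not distorted in this way.

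**The case against.** The strongest defence is that this is a known-groups design and not a continuous sample cut in two at analysis. The Exploratory clinical validation aims ask about differences between elite and novice runners, the real-world section asks whether the devices can tell relevant populations apart, and recruitment is by quota. The group contrast answers that question directly and needs no linearity. This stands: a reader might infer that the ANCOVA should be replaced, and the documents do not support that.

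A reader might also infer that usability suffers the same loss. It does not, because the correlation of SUS scores with age-grade performance is already planned, so the ANOVA is not the only use of performance there.

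Third, the exploratory section opens by promising relationships with performance-relevant measures, the list of demographic variables for gait is open-ended, and the article elsewhere counts age-grade performance among demographics. The percentage may therefore be meant to enter the gait correlations. That is possible, but those correlations are within groups, so even this reading gives no analysis over the whole range.

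Finally, the larger power losses need groups that meet at a cut. The labels may describe well-separated runners, in which case the loss is small. Equally, nothing in the text guarantees separation. The study is an exploratory pilot that quotes no power figure for this contrast, so no stated figure is wrong.

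**Conclusion.** The point holds for the gait outcomes in the real-world arm and only there. The article states no whole-sample analysis of gait on the age-graded percentage, although the score underlies the grouping. Under an approximately linear relation, the group factor alone costs about 16 to 20 points of power at a median cut, about 3 to 9 for outer thirds and about 0.5 to 6 for outer quarters. Without a cut-point or score distribution, the actual loss cannot be placed within that range, and it would be wrong to read the 16 to 20 points as the loss in this trial. The figures rest on assumed correlations of 0.3 to 0.5, a normal score and no covariates. The elite-versus-novice ANCOVA is legitimate and should stay. Priority: optional, a low-cost improvement to an exploratory analysis.

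**What to change.** Keep the recruitment of 20 and 20 and keep the elite-versus-novice ANCOVA. In the Exploratory clinical validation analysis, add for each gait outcome and each device a linear regression on age-graded 5 km percentage across all 40 real-world runners, with the same covariates as the ANCOVA. Report the slope per 10 percentage points with its 95% CI rather than a raw correlation, and show the scatter plot. The SUS analyses need no change on this account.

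The cost is a few lines of text and some extra analysis; no new data, visits or participants are needed. The downside is an assumption of approximate linearity. The scatter plot can check it only where there are data. If the quotas leave a gap between the groups, linearity across that gap cannot be tested, and the report should say so.

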#### System usability scale

Upon immediate completion of the real-world environment testing, participants will be asked to complete the System Usability Scale (SUS) to assess the usability of each of the wearables. The SUS is a simple scale based, multiple-choice questionnaire proposed by John Brooke in 1986 and has been widely adopted in product usability evaluations [36–38]. A final score is provided with interpretation based on a well-established reference standard, with an excellent reliability (0.85) [39]. Overall, the SUS is a quick and simple method for usability evaluation.

### Outcome measures

The primary outcome measures for this study are running gait outcomes as measured by the wearables and are described in Table 2. A secondary outcome measures is usability. Usability refers to the effectiveness, efficiency, and user satisfaction rating of a product (various grades of wearables) in an particular environment by a user for a specific purpose (running gait analysis) [40].

**Table 2 pone.0291289.t002:** The primary outcomes measured by each grade of wearable.

Outcome	Definition	Axivity AX6	DorsaVi ViMove2	DANU Sports System	Reference Measure
** *Spatiotemporal* **					
Ground Contact Time	The time between initial foot contact and toe-off for the same foot	**✓**	**✓**	**✓**	Force plate (overground) and 3D Motion Capture (treadmill)
Step Frequency	The number of steps taken during a given time	**✓**	**✓**	**✓**	3D Motion capture
Step Length	The distance between successive points of initial contact of the opposite foot	X	X	**✓**	3D Motion capture
Step Time	The time between two consecutive heel strikes of the opposite foot	**✓**	X	**✓**	Force plate (overground) and 3D Motion Capture (treadmill)
Foot-Strike Pattern	The way or angle when the foot first contacts the ground	**✓**	X	**✓**	3D Motion capture
Flight Time	The time between toe-off from one foot to initial contact of the other foot	**✓**	X	**✓**	Force plate (overground) and 3D Motion Capture (treadmill)
Symmetry	Any measure of imbalance between the right and left leg	**✓**	**✓**	**✓**	3D Motion capture
** *Kinetic* **					
Tibial Acceleration	Acceleration of the tibia, including peak positive acceleration, gradient, slope, magnitude, loading rate etc.	X	**✓**	**✓**	3D Motion capture

### Sample size calculation

This is the first study (pilot study) to use the novel multi-modal wearable system (DANU system) for gait analysis in any population, alongside other wearables and gold-standard measures. As such, there are few specific previous examples were available to guide estimates for sample size. Previous research that has shown statistically significant outcomes when investigating wearables for running gait assessment in sport have had sample sizes ranging from 1 [41] to 187 [42], with the average number of participants at 26 [21]. Thus, a sample size of 40 participants for analytical validation (i.e., comparison to gold-standards) is feasible and adequately powered [43, 44].

Regarding the exploratory clinical validation analysis, a sample size of 20 participants per group for the performance and clinical group analysis is adequate in this initial exploratory pilot study. While there are no specific rules for sample size calculations in pilot / initial exploratory studies, evidence suggests that 10–12 participants per group may be adequate, and that 20–30 participants per group would be enough to provide valid evidence to draw scientific conclusions [43–46]. Further to this, evidence suggests that to capture 85–90% of use issues 15–20 people per group are required for usability studies [46], therefore our sample of 20 participants per group should be adequate for this initial analysis. Following from the present pilot study, future research can calculate more specific sample sizes and control for relevant variables based on the presented findings.

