Wearable devices offer an alternative to overcome traditional assessment limitations and are becoming increasingly popular amongst runners, coaches and clinicians [17]. Wearables using accelerometers, gyroscopes, and magnetometers, applied individually or in combination as an inertial measurement unit (IMU), and ‘pressure-sensitive’ insoles enable examination of a combination of spatiotemporal, kinetic, and kinematic variables and have become a viable alternative due to their portability and affordability [18]. Wearables can quantify running gait outcomes in any setting (i.e., laboratory, outdoor/real-world), and have the potential to be an effective tool to capture the full duration and nuances of a run, which ultimately may enhance understanding of running performance, fatigue, and injury mechanisms [19, 20].

Wearables have seen an expansive increase in personal use, as well as application in industry and research. However, there is a lack of evidence for validity, reliability, and application of wearables for running gait assessment [19–22], with different grades of devices receiving different levels of testing. For example, many commercial devices receive little / no validation testing before commercial launch, whereas research-grade devices that are developed by academic researchers tend to receive validation testing but may not be applied within relevant populations to inform clinical or performance outcomes [18–22]. Therefore, this pilot study aims to examine the validity, reliability, and application of various grades of wearable devices (research-grade, commercially available and novel multi-modal) for running gait assessment. The presented protocol will follow an evidence-based approach to drive the appropriate adoption of fit-for-purpose wearable technologies [23]. An evaluation of the usefulness and utility is only applicable after gaining evidence and assurance that the underlying data obtain valid and reliable results to answer a given question [23].

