### Statistical analysis

#### Analysis common to all studies

The statistical analysis will be performed using statistical software SPSS 25 (SPSS Inc., Chicago, Illinois, USA). Demographic characteristics will be summarised using descriptive statistics, including mean, standard deviation, median, minimum, maximum, and inter-quartile range for continuous or ordinal data and percentages for categorical data. The descriptive statistics will be tabulated and presented graphically for clarity. All data will be checked for normality distributed with Shapiro-Wilks tests before conducting parametric tests. Non-normal continuous distributions will be transformed where appropriate to meet the requirements of parametric tests; otherwise, the equivalent non-parametric tests will be adopted. Data will also be assessed graphically (such as histograms or scatter plots) for clarity of information. Statistical significance will be determined at p < 0.05 unless otherwise stated. Due to the experimental nature and novelty of the work and wearable systems, we will not control for multiple comparisons in order to avoid a Type II error.

*Analytical validation analysis*. To examine analytical (concurrent) validation of the wearable devices (research-grade, commercial, novel multimodal) for running gait measurement, we will compare outcomes to relevant reference measures (i.e., force plates for ground contact time) in all laboratory testing participants (n = 40). To compare running gait outcomes from the wearables and reference systems, the absolute difference, Pearson’s correlation (r), intraclass correlations (ICC), the level of agreement through the Bland Altman plots, and 95% Limits of agreement (LoA) will be calculated [48]. Accuracy will be evaluated in terms of root mean squared errors (RMSEs).

To determine test re-test reliability of the wearables, r, and ICCs between the two testing time-points will be calculated [49]. A predefined ICC performance scale will be used, defined as poor (<0.50), moderate (0.50–0.75), good (0.75–0.90) or excellent (>0.90) [50]. ICC is a common statistic for evaluating repeatability and is needed to calculate the minimally detectable change (MDC) [51, 52]. The standard error of measurement (SEM) and standard deviation (SD) will also be calculated. Laboratory based analytical validity and reliability outcomes will be descriptively reported and discussed across research-grade, commercial and novel multi-modal wearable devices.

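### The claim that 40 participants is adequate power has no power or precision target behind it, and at n=40 a test-retest ICC graded on its value alone cannot be separated from neighbouring bands when it is moderate or good

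*Protocol article*

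**What the plan says.** The Sample size calculation section deals with two sizes.

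- **Analytical validation.** It reports that "Previous research that has shown statistically significant outcomes when investigating wearables for running gait assessment in sport have had sample sizes ranging from 1" participant upwards (to 187), "with the average number of participants at 26", and from this infers that "a sample size of 40 participants for analytical validation (i.e., comparison to gold-standards) is feasible and adequately powered". Two references follow. No number is taken from them.
- **Group comparisons.** It says that "a sample size of 20 participants per group for the performance and clinical group analysis is adequate in this initial exploratory pilot study", citing a rule of thumb that 10–12 per group may do and that "20–30 participants per group would be enough to provide valid evidence to draw scientific conclusions". More specific sizing is left to later research.

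Under Statistical analysis (Analytical validation analysis), agreement with the reference systems is assessed by absolute difference, Pearson's r, ICC, Bland-Altman limits of agreement and RMSE. For test-retest reliability, "A predefined ICC performance scale will be used, defined as poor" below 0.50, moderate 0.50–0.75, good 0.75–0.90 and excellent above 0.90. The scale is stated for the ICC value, without reference to its uncertainty. Significance is set at p < 0.05 with no multiplicity adjustment.

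**The concern.** Adequate power is a statement about a calculation: a hypothesis or a precision target, and the chance of meeting it. The section contains neither. Studies picked out because they reached significance cannot show that a new study has enough participants, and an average of 26 does not lead to 40.

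The property claimed is also not the one the aims need. ICCs and limits of agreement are estimates, and how many participants are enough depends on how wide their intervals are. If those intervals span two or three grades, a report that one device is good and another moderate may reflect sampling error only. The Discussion expects the study to determine what grade of wearable is needed for real-world running, so readers will use the grades to choose between devices. For the group comparisons, a non-significant result in 20 against 20 could be taken for absence of a difference when the design can show only a large one.

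**Working it through.** **1. The plan's own figure.** The inputs given are a range of 1 to 187 and an average of 26. Neither gives 40, and no effect, SD, planning ICC, power or interval width is stated, so 40 cannot be reproduced.

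**2. ICC precision at n = 40.** From the article: 40 laboratory participants; two sessions, so k = 2; the four-band scale. Assumed: one-way ICC, no dropout, and the observed ICC values below as a range.

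F = (1 + ICC)/(1 − ICC). The limits use F_L = F/F₀.₉₇₅(39, 40) = F/1.8806 and F_U = F × F₀.₉₇₅(40, 39) = F × 1.8854. Each converts back by (F − 1)/(F + 1).

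| Observed ICC | F | F_L | F_U | 95% CI | Bands touched |
|---|---|---|---|---|---|
| 0.75 | 7.00 | 3.72 | 13.20 | 0.58–0.86 | moderate, good |
| 0.80 | 9.00 | 4.79 | 16.97 | 0.65–0.89 | moderate, good |
| 0.85 | 12.33 | 6.56 | 23.25 | 0.74–0.92 | moderate, good, excellent |
| 0.90 | 19.00 | 10.10 | 35.82 | 0.82–0.95 | good, excellent |

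The two-way consistency form changes these by at most 0.01 (for example 0.73–0.92 at an ICC of 0.85).

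**3. Can an interval sit inside one band?** Solve for the observed ICC at which a limit meets a cut-point.

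- *Good:* lower limit 0.75 needs F = 7 × 1.8806 = 13.16, an ICC of at least 0.859. Upper limit 0.90 needs F = 19/1.8854 = 10.08, an ICC of at most 0.819. Both cannot hold.
- *Moderate:* lower limit 0.50 needs F = 3 × 1.8806 = 5.64, an ICC of at least 0.699. Upper limit 0.75 needs F = 7/1.8854 = 3.71, an ICC of at most 0.576. Both cannot hold.
- *Excellent:* lower limit 0.90 needs F = 19 × 1.8806 = 35.73, an ICC of about 0.946. This is attainable.
- *Poor:* upper limit 0.50 needs F = 3/1.8854 = 1.59, an ICC of about 0.23 or less.

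A 95% CI wholly inside the good band first becomes possible at about 65 participants (ICC near 0.84), and inside the moderate band at about 89 (ICC near 0.64).

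**4. Limits of agreement.** With one difference per participant and s the SD of the differences, the half-width of the 95% CI is t₀.₉₇₅(39) × s × √(1/n + 1.96²/(2(n − 1))) = 2.0227 × √(0.0250 + 0.0493) × s = 2.0227 × 0.2725 × s = 0.55 s.

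**5. Group comparisons, 20 against 20.** Two-sided 0.05 (sidedness assumed), unadjusted t test, 38 df, critical t 2.024, noncentrality d × √(20/2) = 3.162 d.

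| d | Noncentrality | Power |
|---|---|---|
| 0.5 | 1.58 | 34% |
| 0.8 | 2.53 | 69% |
| 0.91 | 2.88 | 80% |

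**The case against.** The strongest reply is that this is a pilot. Laboratory results are to be reported descriptively alongside absolute differences, limits of agreement, RMSE, SEM and minimal detectable change, and no device passes or fails on an ICC. The ICC scale belongs to test-retest reliability, whereas the adequacy claim concerns comparison with reference systems. The claim carries two citations, and an article may leave interval reporting to a fuller document. Much of this is fair, and it limits the point. It does not supply a target against which 40 is adequate. Analytical validation is listed apart from the exploratory aims, and both uses of the ICC rest on the same 40 laboratory participants.

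Four stronger readings are tempting but not supported.

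- *That n = 40 cannot grade anything.* An ICC of about 0.946 or more is securely excellent. One-sided power at 0.05 is 84% for 0.75 against a null of 0.50 and 93% for 0.90 against 0.75, though only 55% for 0.85 against 0.75. The point estimate lands in the true band about 77% of the time at a true ICC of 0.80 and 87% at 0.85, but about 50% at a cut-point of 0.75 or 0.90.
- *That the group comparisons are claimed to be adequately powered.* They are called adequate for an exploratory pilot. The sentence about scientific conclusions is a cited rule of thumb, and nothing in the article offers null results as evidence of no difference.
- *That no significance level is given.* It is, at 0.05.
- *That every device-outcome pair enters group testing, against the Introduction's statement that* "An evaluation of the usefulness and utility is only applicable after gaining evidence and assurance that the underlying data obtain valid and reliable results". The article does not say that all pairs enter, and the Discussion places clinical validation after analytical validity and reliability. No breach of sequence is established.

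**Conclusion.** The statement of adequate power is wrong as written, because it names no target and the stated argument cannot provide one. Whether the two citations would help cannot be judged from the article. At n = 40 the design gives ICC intervals about 0.28 wide at 0.75 and 0.13 wide at 0.90. Moderate and good estimates cannot be separated from their neighbours, while very high ICCs can be graded securely. Limits of agreement are known to about ±0.55 SD of the differences. The rule of thumb for 20–30 per group holds, at 20 per group, only for large effects (d of about 0.9 or more).

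These figures rest on assumed ICC and d values, two measurements per participant and complete retest. Losses would widen the intervals a little (at n = 36, an ICC of 0.80 has 0.64–0.89). ANCOVA covariates could raise the power of the group comparisons somewhat. The size of the study is not at fault. What needs changing is the claim made for it and grading by value alone.

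**What to change.** Keep n. In Sample size calculation, replace the claim of adequate power with the expected precision at n = 40: the ICC intervals above and ±0.55 SD for each limit of agreement. For the exploratory group comparisons, state that 20 per group gives 80% power for d of about 0.91, 69% at 0.8 and 34% at 0.5, and that a null result there is not evidence of no difference. Qualify the rule of thumb on scientific conclusions accordingly.

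In Statistical analysis, report a 95% CI with every ICC and every limit of agreement. Assign the ICC grade from that interval, either by its lower limit or as the range of bands it covers, and not from the point estimate alone.

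The cost is wording and routine intervals, with no extra participants. The downside is that some device grades become less favourable, and several may have to be reported as spanning two bands. A new pass mark on the ICC for entry to the group analyses is not needed.
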